#### Analysis of secondary endpoints

Secondary outcomes (i.e., further time points and measures) will be analyzed along the same lines, possibly using MMRM (heterogeneous first-order autoregressive-structured covariance matrix over time) or generalized estimating equation approaches with corresponding marginal means and contrast tests (“multilevel modelling”). Time-to-dropout distributions will be summarized by the Kaplan-Meier method and compared using the (stratified) log-rank test. Adverse events will be aggregated by type, seriousness, intensity and relatedness. All efficacy and safety variables will be summarized by time point and treatment arm (mean, standard deviation, percentiles (i.e., minimum, 25th, 50th, 75th, and maximum), count, percentage). Subgroup analyses will be conducted according to recruitment process, study center and gender (expected male to female ratio of 7:3, thus, meaningful results are expected for boys and girls). Moreover, moderation, mediation and conditional process modelling [104] will be conducted based on regression and structural equations (interaction, simple slope analysis; direct/indirect effects, kappa square). All of the details, particularly regarding how to deal with missing data and attrition, will be documented in a statistical analysis plan.

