### Participant timeline

For ADOPT Online and ADOPT Treatment, the individual study duration per patient is 19 months. Measurements will take place according to a specified schedule. Immediately after the initial investigation (T0, screening), the first measurement (T1) will occur, which involves an examination of inclusion and exclusion criteria. For parents of patients randomized to the experimental group at T1, ADOPT Online will then be carried out over a period of 12 weeks. Measurement T2 will take place 13 weeks after T1. Families that were randomized to TAU after T1 will be offered ADOPT Online at T2. Non-responders to ADOPT Online at T2 (significant symptoms of AD at T2 as rated by the clinician based on parent interview) will subsequently be randomized to either THOPAS or TAU, which will each be carried out over a period of 32 weeks. T3 will occur 32 weeks after T2. The follow-up measurement T4 will take place 32 weeks after T3. Thus, for all patients in ADOPT Online, there will be four study visits (T1-T4). For non-responders to ADOPT Online, who continue treatment in ADOPT Treatment, there will be 24 additional study visits (24 behavior therapy sessions including one intermediate measurement).

For ADOPT Institution, the individual study duration per patient is 16 months. Measurements will take place according to a specified schedule. Immediately after the initial investigation (T0, screening), the first measurement (T1) will occur, which involves an examination of inclusion and exclusion criteria. Children with AD will subsequently be randomized to either THOPAS or TAU, which will each be carried out over a period of 32 weeks. T2 will take place 32 weeks after T1. The follow-up measurement T4 will be conducted 32 weeks after T2. Thus, for all patients in ADOPT Institution, there will be three study visits (T1-T3). For children randomized to THOPAS, there will be 24 additional study visits (24 behavior therapy sessions including 1 intermediate measurement).

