### Sample size

In total, *n* = 597 children will be recruited for ADOPT Online. The community sample will be drawn by ADOPT Epidemiology. A screening tool for AD in children and clinician’s rating in the outpatient sample will then be used to identify the AD and the No AD sample. At T1, inclusion and exclusion criteria will be evaluated for the AD sample, resulting in an estimated sample size of *n* = 497 children, who will be randomized with an allocation rate of 5 (ADOPT Online; *n* = 414) to 1 (TAU; *n* = 83).

In ADOPT Treatment, *n* = 232 children need to be recruited and randomized with an allocation rate of 1 (THOPAS; *n* = 116) to 1 (TAU; *n* = 116). T3 assessment needs to include *n* = 198 patients from the treatment and control group (232 patients minus 34 lost at T3, i.e., 20%). At T4, a total of *n* = 158 patients will be assessed for further follow-up (assuming a further dropout of 20% from T3).

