#### Analysis of primary endpoint

The primary (full) analysis set is derived from the ITT principle (all patients randomized with a valid baseline assessment: ADOPT Online/ADOPT Institution: T1/ADOPT Treatment: T2 and at least one follow-up measurement). The primary outcome measures “change in AD symptoms from T1 to 13 weeks post-randomization (T2)” (ADOPT Online), “change in AD symptoms from T2 to 32 weeks post-randomization (T3)” (ADOPT Treatment) and “change in AD symptoms from T1 to 32 weeks post-randomization (T2)” (ADOPT Institution) will be evaluated by an ANCOVA, with fixed effects baseline, study center, gender and treatment arm and corresponding marginal means and contrast tests (type II sums of squares). Interactions of study center and gender with treatment arm will be explored. Data from study centers with low recruitment (i.e., < 10 patients) will be pooled. The potential clustering of observations of participants by therapist or center will be investigated using multilevel modelling. Multiple imputation approaches will be taken to assess the robustness of the results. Specifically, missing values will be separately imputed by type assuming mixtures of missingness-not-at-random patterns [102]. Imputation data sets will be post-processed by multiplication with factors and addition of offsets (tipping point analysis) [103]. Proxy measures will be taken into account to ameliorate the effects of attrition.

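### The heterogeneous AR(1) covariance named for the secondary MMRM is needlessly restrictive; an unstructured matrix is safer at almost no cost (minor, secondary analyses only)

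*Protocol article*

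**What the plan says.** Under Analysis of secondary endpoints, the protocol article says that further time points and measures will be handled in the same way as the primary endpoint, "possibly using MMRM (heterogeneous first-order autoregressive-structured covariance matrix over time) or generalized estimating equation approaches". The point at issue is the parenthesis in that sentence, the "heterogeneous first-order autoregressive-structured covariance matrix over time". The section closes by deferring to the SAP: "All of the details, particularly regarding how to deal with missing data and attrition, will be documented in a statistical analysis plan".

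The primary model that this refers back to is an ANCOVA "with fixed effects baseline, study center, gender and treatment arm". Baseline is T1 in ADOPT Online and ADOPT Institution, and T2 in ADOPT Treatment.

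Participant timeline gives the spacing for the Online/Treatment sequence: "Measurement T2 will take place 13 weeks after T1", "T3 will occur 32 weeks after T2" and "The follow-up measurement T4 will take place 32 weeks after T3". The visits therefore fall at weeks 0, 13, 45 and 77. ADOPT Institution's main visits are 32 weeks apart throughout. On attrition, Sample size plans ADOPT Treatment's last follow-up "assuming a further dropout of 20% from T3".

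**The concern.** A heterogeneous AR(1) matrix lets the variances differ by visit but has a single correlation, rho, indexed by visit number and not by elapsed time. Two restrictions follow. First, every adjacent pair of visits gets the same correlation, whether 13 or 32 weeks apart. Second, visits two apart get rho squared and visits three apart get rho cubed. Symptom scores in the same child often keep a stable between-child component, and then the correlation does not fall that fast.

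At stake are the follow-up analyses at T3 and T4 and the research question on stability of the treatment outcome. A misfitting covariance distorts model-based standard errors. In a likelihood analysis it also determines how earlier scores stand in for missing later ones, so it can bias the arm difference when dropout depends on earlier scores differently by arm.

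**Working it through.** The plan states no figure for this point, so there is none to reproduce. All true correlations below are assumptions.

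**1. Which gaps enter the model**

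| Trial | Baseline | Post-baseline main visits | Gaps, baseline as covariate | Gaps, baseline in response |
|---|---|---|---|---|
| Online | T1 | T2, T3, T4 | 32/32 | 13/32/32 |
| Treatment | T2 | T3, T4 | 32 | 32/32 |
| Institution | T1 | two, at 32 and 64 weeks | 32 | 32/32 |

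The 13-week gap matters only in ADOPT Online, and only if T1 is a response.

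**2. Covariance parameters for k visits**

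Heterogeneous AR(1) has k + 1; unstructured has k(k + 1)/2.

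- k = 2: 3 and 3, the same model
- k = 3: 4 and 6
- k = 4: 5 and 10

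**3. Standard error of a change contrast, constant true correlation rho, unit variances, complete data**

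The inverse of an AR(1) matrix is non-zero only on the diagonal and between adjacent visits. The best-fitting heterogeneous AR(1) therefore matches the variances and the adjacent correlations, which gives a fitted correlation of exactly rho. A numerical fit at weeks 0, 13, 45 and 77 confirms this. For visits m intervals apart, the true variance of change is 2(1 − rho) and the model's is 2(1 − rho^m). The SE ratio is sqrt[(1 − rho^m)/(1 − rho)].

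- rho = 0.5, two intervals: sqrt(0.75/0.5) = 1.22; three intervals: sqrt(0.875/0.5) = 1.32
- rho = 0.6, two intervals: sqrt(0.64/0.4) = 1.26; three intervals: sqrt(0.784/0.4) = 1.40
- rho = 0.7, two intervals: sqrt(0.51/0.3) = 1.30

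The excess is thus 22-27% over two intervals and 32-40% over three for rho of 0.5 to 0.6. None of it comes from unequal spacing. It applies equally to three visits 32/32 weeks apart.

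**4. The same contrast under pure decay with time (0.5 to 0.7 per 32 weeks), T1 in the Online response**

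Here the 13-week gap is the cause. The T1-T2 change SE is 23-27% too large and the T2-T4 change SE is 6-8% too small.

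**5. Arm differences under dropout**

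This was a large-sample maximum likelihood simulation with 400,000 children per scenario and arm-by-visit means. Dropout was 20% per interval, depending on the last score with logit slope 1.0 in one arm and 0.2 in the other. True correlation was constant, exponential, or random intercept plus decay.

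| Response vector | Last-visit bias, AR(1) | Follow-up SE, model/robust |
|---|---|---|
| Online T1-T4 | 0.04 to 0.075 SD | 1.01 to 1.07 |
| Online T2-T4 | 0 to 0.03 SD | 0.997 to 1.013 |
| Treatment or Institution, baseline included | 0 to 0.04 SD | 1.00 to 1.02 |
| Treatment, two post-baseline visits | same as unstructured | 1.00 |

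Unstructured gave a bias of at most about 0.01 SD, which is simulation noise, and SE ratios of 0.996 to 1.004 throughout. The sign of the AR(1) bias varied: with T1 in the response, T4 bias was −0.075 under constant correlation and +0.05 under exponential decay.

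Two limits apply. Dropout of 20% per interval means 1 − 0.8³ = 49% missing at T4 in the T1-T4 runs and 1 − 0.8² = 36% in the T2-T4 runs. The article states 20% attrition for Online, and its own counts for Treatment give (232 − 158)/232 = 32% at T4, so the bias figures lean high. The T2-T4 runs leave T1 out of the response as a stand-in for a covariate model.

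**6. Scale**

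Against the planned Online effect of 0.378, 0.075/0.378 = 20% and 0.03/0.378 = 8%.

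**The case against.** The strongest objection is that nothing is fixed. The structure sits in parentheses inside a sentence that says possibly and offers GEE as the alternative, and details go to an SAP that is not shown. Covariance choice and fallback rules are ordinary SAP content. This stands as far as it goes: the article names heterogeneous AR(1) but does not commit to it. It is, however, the only covariance structure the article names, and deferring details does not withdraw it.

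The second objection is that handling secondary outcomes like the primary makes baseline a covariate. Post-baseline main visits are then equally spaced in all three trials, and in Treatment and Institution the two structures coincide. This also stands, and it removes the unequal-spacing argument on that reading. It does not remove the forced rho-squared decay across Online's T2, T3 and T4.

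A reader might infer more: that the plan locks in AR(1), and that follow-up standard errors are wrong and estimates biased across the programme because visits are 13, 32 and 32 weeks apart. The documents do not support that. The wording is optional, the 13-week gap belongs to one trial under one model form, and the errors depend on unknown correlations and dropout. The larger percentages concern change contrasts; SEs of arm differences at a visit were at most about 7% too large.

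Multiple imputation with missing-not-at-random patterns and tipping-point analysis are also planned. Separately, Online's T3 and T4 arm comparisons are already altered because TAU families may receive the online training after T2 and non-responders are re-randomised. Covariance choice is a lesser matter there.

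**Conclusion.** The point holds as a minor one. The named structure can misfit for two separate reasons: it ignores elapsed time, which is relevant only to Online with T1 in the response, and it forces geometric decay, which is relevant wherever three or more visits are modelled. With baseline in the response and constant correlation of 0.5 to 0.6, change-contrast SEs are 22-27% too large over two intervals and 32-40% over three. That direction is conservative. Under pure decay in time, some contrasts are instead 6-8% too small. Last-visit bias in Online is about 0.04-0.075 SD with T1 in the response and at most about 0.03 SD without it, under deliberately strong arm-dependent dropout.

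With baseline as a covariate, Treatment and Institution are unaffected on their main visits. If the T1b/T2b questionnaires entered the model this could change, but their timing is not given. No primary analysis is touched. These sizes rest on assumed correlations and dropout, since the article gives no correlation estimates.

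**What to change.** Where an MMRM is used for secondary outcomes, replace the heterogeneous AR(1) with an unstructured covariance over the modelled visits and use Kenward-Roger degrees of freedom. State in advance a fallback used only on non-convergence, for example heterogeneous Toeplitz, or a spatial-power structure in actual weeks with robust standard errors. State also whether baseline is a covariate or part of the response, because that decides how much the choice matters.

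The cost is one or two lines of text and at most five extra covariance parameters (10 against 5 for four visits), which is small with 166 to 497 children randomised per trial. Where only two post-baseline visits are modelled, the change alters nothing.

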As the study designs of ADOPT Online and ADOPT Treatment include a stepped care process, the sample size is defined by the expected effect sizes of the ADOPT Treatment step. The effect sizes found in the reported meta-analyses of trials on the effects of mostly standardized treatments in a group format (mostly compared with waiting list control) are in the range of *d* = 0.3 to 0.6. The effect sizes of personalized individual treatments tend to be elevated, in the range of 0.6 to 0.8 [51, 98]. The planned trial will be conducted with online treatment-refractory AD and may therefore comprise a more severe group of patients, who may be harder to treat. Thus, a moderate effect size of *d* = 0.5 is expected. The two-sample *t*-test with an allocation ratio of 1:1 (THOPAS: TAU) requires 64 patients per group in order to attain a power of 80% at a two-sided significance level of 5%. A similar therapist effect (due to clustering) as in [99] yields a design effect of 1.4 (intraclass correlation 0.1, five patients per therapist on average); thus, *n* = 179 [128*1.4] patients are required [100]. Further accounting for heterogeneous cluster sizes (+ 10%) and attrition (+ 15%) yields approximately *n* = 232 patients to be randomized (*n* = 116 to THOPAS, *n* = 116 to TAU). Note that power is further increased by taking a baseline-adjusted analysis of covariance (ANCOVA)/mixed model for repeated measures (MMRM) approach for statistical analysis. We expect a male:female ratio of 7:3 [51]. Thus, the sample size of ADOPT Treatment is set at *n* = 232, with *n* = 116 in the treatment arm and *n* = 116 in the control group.

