Meta-analyses of self-help PMT report effect sizes between 0.61 and 1.01 [25, 27], with smaller effects for self-help interventions with no therapist contact. It remains unclear whether symptom severity serves as a moderator favoring severely affected children in PMT [22]. Breitenstein [27] reported mean completion rates of about 78% in their meta-analysis on online PMT. In studies on self-help PMT, dropout ranged between 5 and 30% [28, 56]. On the other hand, for highly burdened parents, like those in our AD sample, online interventions might be harder to successfully complete. Given this, and the fact that online PMT without therapist contact is already less effective than telephone-assisted self-help interventions, a small effect size such as 0.378 should be expected for ADOPT Online. Thus, the two-sample t-test with an allocation ratio of 5:1 (ADOPT Online: TAU) requires 331 and 66 patients, respectively, to attain a power of 80% at a two-sided significance level of 5%. Further accounting for 20% attrition yields about *n* = 497 [≈ 397/0.8] patients to be randomized (*n* = 414 to ADOPT Online, *n* = 83 to TAU). Note that power is further increased by taking a baseline-adjusted ANCOVA/MMRM approach for statistical analysis. We expect a male:female ratio of 7:3 [51]. Missing data and non-compliance will be dealt with by performing intention-to-treat (ITT) analysis.

In ADOPT Institution, a screening tool for AD in children will then identify the AD (*n* = 166) and the No AD (*n* = 80) sample in a total of *n* = 750 children in OHC. According to the cut-off developed in ADOPT Epidemiology, we expect that at least 25% of the screening sample will be identified as screening-positive. Since the institutions have already agreed to take part in the project, we expect that most of the children screened positive will participate in the intervention. A total of *n* = 166 children need to be recruited and randomized with an allocation rate of 1 (THOPAS) to 1 (TAU) (83 to the experimental treatment, 83 to TAU). T2 assessment needs to be conducted with *n* = 140 patients from the treatment and control group (166 patients minus 26 lost at T2, i.e., 20%) and 64 from the No AD group. At T4, a total of 169 patients will be assessed for further follow-up (assuming a further dropout of 20% from T2).

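### The 7:3 sex ratio does not support the expectation of meaningful results in both boys and girls: each trial is sized for the whole sample only, and power in girls is about 33% to 53% under plausible assumptions

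*Protocol article*

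**What the plan says.** Analysis of secondary endpoints lists subgroup analyses by recruitment process, study center and gender. For gender it gives the expected 7:3 ratio as a reason and draws a conclusion from it: "thus, meaningful results are expected for boys and girls".

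The Sample size section repeats the same split for all three trials ("We expect a male:female ratio of 7:3") and sizes each one on a two-sample t-test in the whole sample, at 80% power and two-sided 5%:

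- ADOPT Treatment: "a moderate effect size of *d* = 0.5 is expected", 64 per group.
- ADOPT Online: "a small effect size such as 0.378 should be expected for ADOPT Online", 331 and 66 at 5:1.
- ADOPT Institution: d = 0.6, 45 per group.

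Treatment and Institution are then inflated for therapist clustering (design effect 1.4, from an intraclass correlation of 0.1 and five patients per therapist), uneven cluster sizes and attrition. Online is inflated for attrition only. The section adds that baseline-adjusted ANCOVA or MMRM raises power further, but gives no figure. No power or precision is given for either sex.

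Analysis of primary endpoint says that the interaction of gender with treatment arm will be explored. Analysis of secondary endpoints also plans moderation modelling with interaction terms.

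**The concern.** The sentence asserts a property of the design, and the only reason it gives is the sex ratio. A 7:3 split of a sample that just reaches 80% power as a whole argues against separate conclusions in the smaller group.

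What is at stake is how results by sex will be read. If the effect is the same in boys and girls and equals the planned value, a significant result in boys beside a non-significant one in girls is a common outcome. With power of 0.65 and 0.33, and treating the two estimates as independent, its probability is 0.65 × 0.67 = 0.44. Both are significant with probability 0.65 × 0.33 = 0.21. A protocol that announces in advance that each sex will give meaningful results makes it easier to misread that pattern as a difference in effect.

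**Working it through.** **1. Whole-trial figures.** Noncentral-t power at the stated sizes is 80.1% for Treatment (64/64, d = 0.5), 79.9% for Online (331/66, d = 0.378) and 80.4% for Institution (45/45, d = 0.6). The article's sizing reproduces.

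**2. Power by sex on the article's own basis.** Each arm's effective size is multiplied by 0.3 or 0.7, with d and alpha unchanged. The noncentrality is d × √(n₁n₂/(n₁+n₂)).

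| Trial | Girls per arm | Power, girls | Boys per arm | Power, boys |
|---|---|---|---|---|
| Treatment | 19.2 / 19.2 | 32.6% | 44.8 / 44.8 | 64.8% |
| Online | 99.3 / 19.8 | 33.1% | 231.7 / 46.2 | 64.7% |
| Institution | 13.5 / 13.5 | 32.3% | 31.5 / 31.5 | 64.9% |

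The effect detectable in girls with 80% power is d = 0.93, 0.70 and 1.12, against planned effects of 0.5, 0.378 and 0.6. The expected 95% confidence interval half-width in girls, t × √(1/n₁ + 1/n₂), is 0.65, 0.49 and 0.79 SD. Each exceeds the planned effect.

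**3. Smaller same-sex clusters (Treatment and Institution).** Five patients per therapist means 5 × 0.3 = 1.5 girls and 5 × 0.7 = 3.5 boys. The design effect is then 1 + 0.1 × 0.5 = 1.05 for girls and 1 + 0.1 × 2.5 = 1.25 for boys. The 15% attrition and 10% cluster-size allowances are kept.

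- Treatment, girls: 232 × 0.85 × 0.9 × 0.3 / 1.05 / 2 = 25.4 per arm, power 41.5%. Boys: 49.7 per arm, 69.4%.
- Institution, girls: 166 × 0.85 × 0.9 × 0.3 / 1.05 / 2 = 18.1 per arm, power 41.9%. Boys: 35.6 per arm, 70.4%.

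**4. Baseline adjustment.** The article gives no baseline correlation r, so r is an assumption here. ANCOVA is represented by replacing d with d/√(1 − r²).

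| Assumed r | Girls, sizes of step 2 | Girls, sizes of step 3 | Boys, sizes of step 2 | Boys, sizes of step 3 |
|---|---|---|---|---|
| 0 | 32–33% | 42% | 65% | 69–70% |
| 0.3 | 35–36% | 45% | 69% | 74% |
| 0.5 | 41–42% | 52–53% | 77% | 81–82% |
| 0.7 | 56–57% | 69% | 91% | 93–94% |

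Step 3 sizes apply to Treatment and Institution only. Girls reach 80% power only at r of about 0.84 on step 2 sizes, for example Treatment: √(1 − (0.5/0.93)²) = 0.84. On step 3 sizes they need about 0.78: 0.5/√(1 − 0.78²) = 0.80, which with 25.4 per arm gives 80%.

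**5. Clustering and attrition ignored.** Counting every randomized child, unadjusted power in girls is 54% (Treatment), 40% (Online) and 55% (Institution).

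**6. Interaction.** Its standard error is √(1/0.3 + 1/0.7) = 2.18 times that of the main effect. For Treatment, on step 2 sizes, the main-effect standard error is √(2/64) = 0.177, so the interaction's is 0.386. An interaction of 0.5 gives z = 1.30 and power of 25%. Online and Institution give 25% and 26%.

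**The case against.** Four points can be made for the plan.

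- **The planned test is ANCOVA, not a t-test, and same-sex clusters are smaller.** This stands. A reader might infer that each trial simply has 33% power in girls and 65% in boys. The documents do not support those as fixed properties. They are unadjusted figures, and in Treatment and Institution they also carry a design effect meant for the full therapist caseload. For boys, the shortfall may vanish.
- **The right tool is already planned.** This also stands. Gender stratifies randomization, is a term in the primary model and is listed as a moderator, and its interaction with treatment is to be explored. A reader might infer that the plan intends separate significance claims in boys and girls. No section says so. The interaction itself is weakly powered, however, so it will not settle the question alone.
- **The word meaningful does not promise 80% power.** It could mean only that neither sex is too sparse to report. Partly fair, since the article sets no power standard for subgroups. But the sentence draws a conclusion from the ratio, and on the unadjusted basis the expected interval in girls is wider on each side than the planned effect.
- **The analyses are secondary, with details left to the SAP.** True, and it limits the weight of the point. The objection here is to a stated claim, not to missing detail.

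**Conclusion.** The inference from the 7:3 ratio does not hold for girls. At the planned effects, power in girls is about 33% on the article's own basis and about 42% in Treatment and Institution with cluster-adjusted design effects. It is about 41% to 53% at an assumed baseline correlation of 0.5, and below 70% at an assumed 0.7. Only correlations near 0.8 or above would bring it to 80%.

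For boys, the claim cannot be rejected. Power is about 65% to 70% unadjusted and about 77% to 82% at an assumed correlation of 0.5.

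These figures assume the planned effect in both sexes, the expected 30% of girls and the article's intraclass correlation. It would go too far to infer that the trials are undersized or that the primary analysis is affected: the whole-sample sizes reproduce, and no primary test or decision depends on the sentence. This is a wording change that should be made, preferably before results by sex are seen.

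**What to change.** - Delete the clause, or qualify it so that the sex ratio is no longer offered as a reason to expect meaningful results in girls.
- State that conclusions about sex differences rest on the treatment-by-gender interaction already planned, reported with its confidence interval, and note its limited power.
- State that within-gender effects are descriptive: estimate and confidence interval, with no separate significance claims.
- Give expected power or precision by sex as a range, naming the assumed baseline correlation and the within-sex design effect. The unadjusted 33% and 65% should not be printed as the trials' power.

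Sample size, conduct and primary analysis stay as they are. The only cost is a less favourable stated expectation for the gender subgroups.
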